##### Cognitive Function

The Childhood Executive Functioning Inventory (CHEXI) (41) will be used to evaluate the executive function of the preschoolers. The CHEXI consists of 24 items in two domains: working memory (13 items) and inhibition (11 items). For each item, five options ranging from “1 = definitely not true” to “5 = definitely true” are provided, where a higher score indicates worse executive function. The CHEXI has demonstrated high reliability and has been translated into traditional Chinese (42). It can be downloaded freely online (https://chexi.se/onewebmedia/CHEXI-TraditionalChinese2016.pdf).

##### Covariates

Preschoolers' characteristics (age, sex, number of siblings), parents' characteristics (age, sex, height, weight, education level), family income, family size, family structure, and type of residence will be reported by parents. Children's eating habits will be measured using questions based on a previous study conducted among preschoolers in Hong Kong (43). Five domains (fruit, vegetables, dairy products, breakfast, high-energy-density foods) will be covered using five items. Responses to all items will be made on a 5-point Likert scale. For example, breakfast intake will be assessed using one question: How often does your child eat breakfast? Possible answers will be as follows: <1 day/week, 1–2 days/week, 3–4 days/week, 5–6 days/week, and every day. Possible answers for the other questions will be <1 serving/day, 1–2 servings/day, 3–4 servings/day, 5–6 servings/day, and >6 servings/day.

##### Feasibility and Acceptability

**Feasibility**. Retention rates for each group and reasons given by participants who remove, withdraw, or are lost to follow-up will be recorded. Adverse effects, if any, will be documented.

**Fidelity and Adherence**. Intervention fidelity will be monitored, including the delivery of three workshops, six educational materials, two brief reports of measurements, and five questionnaires and reminders (one brief questionnaire every 2 weeks) for each person (24).

**Acceptability**. Based on a previous study (17), five items will be used to separately measure the PA and SB components for the two intervention groups. For the integrated approach, an additional five items will be used to evaluate the sleep component. Among the five items for each component, one item will be used to evaluate the overall intervention (poor, average, or good). The other four items will be used to evaluate each strategy separately (i.e., educational material, workshop, report of measurements, interactive questionnaire and reminder about material use). Parents will be asked to rate the usefulness using 5-point Likert scales (from “1 = not useful” to “5 = very useful”).

### Randomization and Blinding

Randomization and group assignment will be conducted using computer-generated random numbers by a third person who is blinded to the purpose of the study. After baseline data collection, the participants will be randomly allocated to one of three arms. The trained staff who will be responsible for data collection will also be blinded to group assignment. Although blinding participants to the intervention is not feasible for this study, families in the two intervention groups will not be disclosed of the differences in the intervention contents.

### Statistical Methods

Analyses will be performed using SPSS 27.0. The significance level will be set at 0.05. Descriptive statistics will be presented for the children's baseline movement behaviors. Feasibility and acceptability will be presented using percentages. Differences in movement behaviors across three groups at baseline will be assessed using analysis of covariance. The intention-to-treat principle (all participants) and sensitivity analysis (participants with complete data) will be used to compare primary outcomes between groups. Generalized estimating equations will be applied to examine the effects of the intervention (PA + SB group vs. control group, PA + SB + sleep group vs. control group) on primary outcomes (children's overall movement behaviors, total PA, MVPA, sedentary time, screen time, sleep duration) and secondary outcomes, adjusting for covariates. Also, the difference of the effect between two intervention groups (PA + SB group vs. PA + SB + sleep) will be examined using generalized estimating equations.

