### Sample Size

A recent systematic review and meta-analysis found a small but statistically significant effect size for interventions to increase PA in children under 5 years old (11). Intervention studies aiming to reduce SB and improve sleep hygiene among young children reported small to medium effect sizes (17, 24). Based on the above information, a prior analysis was conducted, which indicates that a minimum sample size of 99 (33 per group) is required to detect a small effect size *f* of 0.15 with a power of 0.90 under the conditions of an alpha level of 0.05, three arms (PA + SB group, PA + SB + sleep group, wait-list control group), and four repeated measures assuming a correlation between repeated measures at 0.50. Considering a potential attrition rate of 20% (25, 26), 119 children are needed. Therefore, using an over-sampling procedure, 150 parent-child dyads will be recruited and screened. The power calculation is conducted using G^*^Power 3.1.9.7.

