### Intervention

#### Procedure

Data collection will be performed during a school visit at baseline (T1), 6 weeks (mid-term; T2), 12 weeks (immediately after the intervention; T3), and 24 weeks (follow-up; T4). Accelerometers and a take-home package will be distributed to parents via the children. The package will include (1) an information sheet about the ActiGraph and instructions on how to wear the device during the 7-day period; (2) online questionnaires to be completed by parents (assessing parents' PA, SB, screen time, and sleep, children's screen time and sleep quality, and demographic information); (3) a log sheet for parents to record when the device is removed and the reasons for removal and their child's nap time. After the baseline and mid-term measurements, a brief report will be provided to parents, including the current movement behaviors of their child and the differences from the recommended durations. After the final measurement (T4), a complete report presenting the changes in the child's movement behaviors will be provided to each parent.

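### The covariates listed for the GEE omit the baseline value of the outcome, and its role in the model is not stated; adjusting for it would gain precision cheaply, and the between-arm baseline test should go

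*Protocol article*

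**What the plan says.** Three parts of the protocol article bear on this point.

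- **Statistical Methods.** Baseline is compared between arms: "Differences in movement behaviors across three groups at baseline will be assessed using analysis of covariance". The effect analysis follows: "Generalized estimating equations will be applied to examine the effects of the intervention" on the primary "and secondary outcomes, adjusting for covariates". The contrasts are each intervention arm against control and the two intervention arms against each other. No visit term, arm-by-visit term or baseline term is described.
- **Covariates (under Outcomes).** The list reads "Preschoolers' characteristics (age, sex, number of siblings), parents' characteristics (age, sex, height, weight, education level), family income, family size, family structure" and type of residence, and then: "Children's eating habits will be measured using questions based on a previous study conducted among preschoolers in Hong Kong". The T1 value of the outcome is not on it.
- **Sample Size.** The calculation uses f = 0.15, power 0.90, alpha 0.05, three arms and "four repeated measures assuming a correlation between repeated measures at 0.50", and gives 99 children (33 per group). The Procedure section shows that the four measures are T1 (baseline), T2 (6 weeks), T3 (12 weeks) and T4 (24 weeks).

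The Randomization and Blinding section places allocation after baseline data collection.

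**The concern.** A child's own T1 value is usually among the strongest predictors of the later values of the same outcome. The plan itself assumes a correlation of 0.50 between any two occasions. A treatment contrast that does not condition on T1 carries variance that could be removed with data already collected. What is at stake is precision in the pairwise contrasts, including integrated against daytime-only, which is the third hypothesis.

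The planned baseline comparison does not fill this gap. Children are randomized after baseline, so any difference between arms at T1 is due to chance, and a test of it answers no question. A chance imbalance in T1 is properly dealt with by adjustment, whatever a test shows.

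**Working it through.** **Inputs.** From Sample Size: f = 0.15, alpha = 0.05, k = 3 arms, m = 4 measures, correlation ρ = 0.50, N = 99. From Procedure: one baseline and three follow-up visits. Assumed here: unit variance at each visit and the same correlation between every pair of visits (compound symmetry).

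**Step 1: reproduce the plan's figure.** For a group-by-time interaction, λ = f²·N·m/(1 − ρ) = 0.0225 × 99 × 4 / 0.5 = 17.82, with df1 = (3 − 1)(4 − 1) = 6 and df2 = (99 − 3)(4 − 1) = 288. Power is 0.9003, and 99 is the smallest multiple of 3 that reaches 0.90. Neither of the other two forms tried gives 99: a within-factor main effect needs 81 and a between-factor main effect needs 357. The sample size therefore rests on a group-by-time test in which T1 is one of the four measures.

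**Step 2: variance of the treatment contrast under three models.** For the mean of q follow-up visits, up to the common factor 2/n (n children per arm):

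- post-baseline visits only: v = (1 + (q − 1)ρ)/q
- change from baseline (group-by-time with unconstrained baseline means): v + 1 − 2ρ
- adjusted for T1: v − ρ²

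| ρ | Follow-up | Post-only | Change | Adjusted | Saving vs post-only | Saving vs change |
|---|---|---|---|---|---|---|
| 0.3 | one visit | 1.0000 | 1.4000 | 0.9100 | 9.0% | 35.0% |
| 0.3 | mean of T2–T4 | 0.5333 | 0.9333 | 0.4433 | 16.9% | 52.5% |
| 0.5 | one visit | 1.0000 | 1.0000 | 0.7500 | 25.0% | 25.0% |
| 0.5 | mean of T2–T4 | 0.6667 | 0.6667 | 0.4167 | 37.5% | 37.5% |
| 0.7 | one visit | 1.0000 | 0.6000 | 0.5100 | 49.0% | 15.0% |
| 0.7 | mean of T2–T4 | 0.8000 | 0.4000 | 0.3100 | 61.3% | 22.5% |

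At ρ = 0.50 the two unadjusted models have equal variance because 1 − 2ρ = 0. The saving there equals that from 1/0.75 = 1.33 or 0.6667/0.4167 = 1.60 times as many children.

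**Step 3: check by generalized least squares.** With 33 per arm and ρ = 0.50, an unconstrained group-by-time model on T1 to T4 gives contrast variances of 0.0606 (one visit) and 0.0404 (mean of three). Constraining the baseline means to be equal gives 0.0455 and 0.0253. The ratios are 0.75 and 0.625, in agreement with step 2.

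**Step 4: overlap with the listed covariates.** Suppose these already explain a share R² of the variance at every visit. The remaining correlation is then (0.5 − R²)/(1 − R²).

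- R² = 0.10 (assumed): remaining correlation 0.444; saving against post-only 19.8% (one visit) to 31.4% (mean).
- R² = 0.30 (assumed): remaining correlation 0.286; saving against post-only 8.2% to 15.6%.

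Against the change model the saving does not shrink: it is 27.8% to 41.7% at R² = 0.10 and 35.7% to 53.6% at R² = 0.30.

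**Step 5: illustration in power.** Power = Φ(d/√(2v/n) − 1.96). The standardized difference d = 0.5 and n = 40 per arm are assumptions, not protocol figures. Power rises from 0.61 to 0.73 at one visit and from 0.78 to 0.93 for the mean of T2 to T4. With an assumed d = 0.3 and the plan's 33 per arm, it rises from 0.23 to 0.29 and from 0.32 to 0.47.

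**The case against.** The strongest reply is that the article never says T1 is left out. It gives no model terms, and a condensed article may leave them to an analysis plan. The Covariates section sits under Outcomes and describes additional parent-reported measures; T1 movement behaviors are already described as outcomes, so their absence from that list proves little. The four-measure sample size even suggests that T1 is in the outcome vector and so is used.

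Much of this stands. A reader might infer that the plan excludes baseline from the GEE; the documents do not establish that, and the point is put conditionally for this reason. But the article does set out its covariates under that name and then adjusts for covariates, so the text as it stands leads to a model without T1 adjustment. Having T1 in the outcome vector does not by itself recover the precision: step 3 shows the same loss unless the baseline means are constrained.

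Four other strong readings also fail:

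- **A fixed loss of 25% to 37.5%.** That range belongs to ρ = 0.50, compound symmetry and no covariate overlap.
- **An underpowered trial.** The stated 99 reproduces at 0.90 for the test it was built on, and the effect sizes in step 5 are assumed.
- **T1 available for every randomized child, so that adjustment has no downside.** The accelerometer rules require at least 3 valid days including a weekend day, and nothing says that a child with invalid T1 wear or a missing T1 questionnaire is not randomized.
- **Harm to the treatment estimate from the baseline test.** It is uninformative, but no section makes the choice of covariates depend on its result.

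**Conclusion.** The point holds as a worthwhile and nearly free improvement. The listed covariates omit the T1 outcome value and the role of T1 is unstated. Under either a post-only model or an unconstrained group-by-time model, the treatment contrasts have more variance than they need. At the plan's own correlation the avoidable part is 25% at a single visit and 37.5% for the T2 to T4 mean. Without covariate overlap, the saving runs from about 9–17% (ρ = 0.3) to 49–61% (ρ = 0.7) against post-only, and from 35–53% down to 15–23% against change. At ρ = 0.50, covariates that explain an assumed 10% or 30% of variance reduce the saving against post-only to 20–31% or 8–16%. This is a loss of precision only. The conclusion that the between-arm baseline test can show only chance differences needs none of these assumptions.

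**What to change.** In Statistical Methods, state one of two models:

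- a GEE fitted to T2, T3 and T4 with arm, visit, arm-by-visit and the T1 value of the same outcome (interacted with visit) as a covariate, besides the listed covariates; or
- a GEE that keeps T1 as an outcome and constrains baseline means to be equal across arms. This version needs a working correlation other than independence, because under independence its follow-up contrasts fall back to the post-only ones.

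Say how children with a missing or invalid T1 value are kept: by the constrained-baseline model, or by imputing T1 in the covariate model. Otherwise the covariate model would drop them and the all-participants analysis would be lost. Replace the between-arm baseline test with descriptive statistics by arm.

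The cost is a change of wording and a rule for missing T1 values. No new data are needed.

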##### Compositional Data

Compositional data analysis has been suggested to examine movement behaviors occurring within a finite period, specifically when they are continuously measured using accelerometers (31). The time spent on one movement behavior relative to all other behaviors will be presented as isometric log-ratio coordinates (*ilr*), which will be the outcome variable in the regression models. For example, a 24-h period can be divided into time spent in PA, SB, and sleep. Taking PA as an example, the equation is as follows:

$$\begin{array}{l} ilr_{1}=\sqrt{\frac{2}{3}}\ln\left(\frac{PA}{\sqrt[{2}]{SB^{*}Sleep}}\right) \end{array}$$

where *ilr*_1_ represents sleep relative to all other movement behaviors.

The time allocated to SB relative to other movement behaviors can be assessed using the *ilr*_2_, which can be expressed as follows:

$$\begin{array}{l} ilr_{2}=\sqrt{\frac{2}{3}}\ln\left(\frac{SB}{\sqrt[{2}]{PA^{*}Sleep}}\right) \end{array}$$

Similarly, the time allocated to sleep relative to other movement behaviors can be assessed using *ilr*_3_, which can be expressed as follows:

$$\begin{array}{l} ilr_{3}=\sqrt{\frac{2}{3}}\ln\left(\frac{Sleep}{\sqrt[{2}]{PA^{*}SB}}\right) \end{array}$$

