## Discussion

The aim of the proposed study will be to explore the impact of an integrated movement behaviors (PA + SB + sleep) intervention on promoting overall 24-h movement behaviors (based on activity sleep index and compositional data) and to evaluate how changes in overall 24-h movement behaviors mediate the effect of interventions on health outcomes among preschoolers. At the time this study was initiated, to the best of our knowledge, no studies have examined the effect of an intervention targeting change in all 24-h movement behaviors among preschoolers.

Engaging in a healthy combination of movement behaviors has been related to health among young children (1). In Hong Kong, low compliance with the WHO 24-h movement guidelines among preschoolers has been reported, suggesting the need for interventions aimed at improving all three behaviors (7). Although previous interventions have been demonstrated to be effective in improving individual behaviors among preschoolers (11–13), no study has simultaneously targeted all three 24-h movement behaviors using integrated strategies for the early years. To fill this gap, the proposed intervention will target all three behaviors, and we will examine how these behaviors change as a whole. Two indicators—an activity sleep index and compositional behavior data—will be used to examine preschoolers' overall behaviors. The activity sleep index provides a total score for different dimensions of movement behaviors, with a higher score indicating better overall movement behaviors (27). This indicator may therefore better reflect the overall pattern of 24-h movement behaviors (total PA, MVPA, screen time, and duration and timing of sleep) and can provide insight into how different behaviors change simultaneously. The other primary outcome will be compositional data that reveal the time spent on one behavior relative to other behaviors, which has been increasingly used (31). Previous studies have used compositional data analysis when examining 24-h movement behaviors and health outcomes among preschool-aged children, but most of them applied cross-sectional designs and measured sleep duration subjectively (44–47). Therefore, an intervention study adopting device-based measurement is needed to objectively explore the effect on compositional behavior data in this age group.

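### Six or more unranked primary outcomes, each compared in three contrasts at 0.05, with a sample size built on one omnibus test and no joint test of the composition

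*Protocol article*

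**What the plan says.** All references are to the protocol article.

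- **Statistical Methods** lists the primary outcomes as the children's "overall movement behaviors, total PA, MVPA, sedentary time, screen time, sleep duration". Generalized estimating equations (GEE) compare the dyadic arm with control, the integrated arm with control, and the two active arms with each other. On error control the section says only: "The significance level will be set at 0.05".
- **Abstract** introduces the primary outcomes as examples, so its list is open-ended.
- **Discussion** describes overall behavior through two indicators. It takes the activity sleep index first and then says: "The other primary outcome will be compositional data that reveal the time spent on one behavior relative to other behaviors". That reads as two primary outcomes.
- **Sample Size** uses a single calculation: effect size f "of 0.15 with a power of 0.90 under the conditions of an alpha level of 0.05", three arms, and "four repeated measures assuming a correlation between repeated measures at 0.50". It concludes that "a minimum sample size of 99 (33 per group) is required".
- **Compositional Data** defines three coordinates, each setting one of PA, SB and sleep against the geometric mean of the other two, as regression outcomes. The first has PA in the numerator, but the text says that it "represents sleep relative to all other movement behaviors".

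**The concern.** The second and third hypotheses in the Introduction are that both approaches change behaviors effectively and that the integrated approach is superior. Neither says on which outcome this will be judged. With an unranked list, a single favourable result among many could be presented as a primary finding, while the trial was sized as though there were one test. The primary set also differs between the Abstract, Statistical Methods and Discussion, so any later adjustment rule would have no agreed family to act on.

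For the composition, the Introduction faults the only earlier study of all three behaviors for not evaluating change as a whole, and the Discussion promises to do so. Three one-versus-rest regressions do not test that.

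**Working it through.** **1. The plan's own figure.** Inputs from Sample Size: f = 0.15, k = 3 arms, m = 4 measures, ρ = 0.50, α = 0.05. The G*Power group-by-time interaction model, with sphericity assumed, has

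- λ = f²·N·m/(1 − ρ) = 0.0225 × 99 × 4/0.5 = 17.82
- df₁ = (k − 1)(m − 1) = 6
- df₂ = (N − k)(m − 1) = 96 × 3 = 288

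Power is 0.900 at N = 99 and 0.889 at N = 96, so 99 reproduces. The within-subject variant gives 81 and the between-group variant 357; neither matches. The trial is therefore sized for one omnibus interaction test on one outcome.

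**2. Number of comparisons.** Six listed outcomes × three contrasts = 18. Counting the index and the composition separately gives 7 × 3 = 21. I use 18 as the firm minimum.

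**3. Chance of at least one false positive when no arm differs.** For independent tests it is 1 − 0.95¹⁸ = 0.60. The contrasts share arms and the outcomes are related, so I simulated six equally correlated outcomes in three arms, with all three contrasts at |z| > 1.96. The correlations are assumptions, because the article gives none.

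| Outcome correlation | At least one of 18 |
|---|---|
| 0 | 0.54 |
| 0.3 | 0.50 |
| 0.5 | 0.44 |
| 0.7 | 0.35 |

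One outcome with three contrasts gives about 0.12.

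**4. By hypothesis.** This assumes that success on any one of the six outcomes would be enough.

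- *Integrated versus dyadic, two-sided:* 1 − 0.95⁶ = 0.265 at correlation 0, falling to 0.16–0.17 at 0.7.
- *Integrated versus dyadic, favourable direction only:* 1 − 0.975⁶ = 0.14 at correlation 0, falling to 0.08 at 0.7. The nominal one-sided level is 0.025.
- *Both active arms beat control, favourable direction:* 0.04 falling to 0.02.

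**5. Power if several primaries are kept.** The same interaction model at Bonferroni levels, which is also Holm's first step, gives:

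| Tests | Level | Power, N = 99 | Power, N = 120 |
|---|---|---|---|
| 1 | 0.05 | 0.90 | 0.95 |
| 6 | 0.0083 | 0.73 | 0.84 |
| 18 | 0.0028 | 0.60 | 0.75 |

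N = 120 is 150 × (1 − 0.20), if all 150 dyads are randomized.

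**6. The coordinates.** Each is √(2/3) × [ln(one part) − ½(sum of the logs of the other two)]. In the sum of the three, every log appears once with weight 1 and twice with weight −½, so the total is 0 for every child. For illustration, PA 240, SB 570 and sleep 630 min give −0.747 + 0.312 + 0.435 = 0. The three coordinates carry two dimensions.

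**The case against.** The strongest reply is that this is a journal article. An adjustment method, a testing order and a primary time point are commonly left to an analysis plan, and the article does not say that there will be no adjustment. That is fair for the method of adjustment. It does not cover the set of primary outcomes, which the article itself fixes and describes in three different ways, or the sample size, which it ties to one test at 0.05.

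Three stronger readings are tempting, and the document does not support them.

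- *Every visit is tested separately.* There are three post-baseline visits and no named primary time point, which would suggest 54 tests or more. But the text says only that GEE will be used, and N = 99 reproduces as an omnibus interaction over time. I claim no count above the outcomes and contrasts stated.
- *A positive conclusion is likely even with no effect.* The 0.35 to 0.54 includes results in either direction on any contrast. False favourable claims matched to the hypotheses are much rarer (step 4), and no any-one-test decision rule is written down. The inflation is real, but likely is too strong.
- *The three coordinate regressions are invalid.* They are not. Modelled one at a time, each validly answers how one behavior changes relative to the rest, and the article neither calls them independent nor enters all three in one model. The Discussion also assigns overall change to the index as well as the composition. What remains is that no joint test of the composition is described, although change as a whole is an aim.

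The label on the first coordinate is a slip: the sentence before the formula announces PA.

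**Conclusion.** The point holds. The article fixes at least six primary outcomes (seven or more on its own definitions) and three contrasts at 0.05 without ranking, contradicts itself on how many are primary, and sizes the trial for one omnibus test. The chance of at least one false positive over the 18 comparisons is about 0.35 to 0.54. For the superiority contrast alone it is about 0.16 to 0.27 two-sided, or 0.08 to 0.14 in the favourable direction. These ranges assume equal outcome correlations between 0.7 and 0, no true difference, one test per outcome and contrast, and no adjustment elsewhere. The hypothesis-level figures also assume that any one outcome would suffice. The zero-sum result for the coordinates is exact. Its consequence is limited to the missing whole-composition test, and the mislabelled coordinate is minor.

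**What to change.** 1. Reconcile the Abstract, Statistical Methods and Discussion. Either name one primary outcome and time point (for example the activity sleep index at T3, 12 weeks) with a prespecified order for the three contrasts, or keep several primaries and apply Holm across them. Which outcome and which order is the sponsor's choice.
2. Make the other behaviors secondary, reported as estimates with confidence intervals.
3. Test the composition with one joint 2-df test of an orthonormal coordinate pair per contrast. Keep the one-versus-rest coordinates to describe direction.
4. Correct the label of the first coordinate from sleep to PA.
5. Restate the power for the test actually chosen.

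**Cost.** With one primary outcome, some behaviors lose primary status, and a contrast late in a fixed order is tested only if those before it succeed. The level stays at 0.05, but the stated 0.90 belongs to the omnibus interaction. For a pairwise contrast at T3 with 40 completers per arm (120/3) and an assumed baseline correlation of 0.5, 90% power needs a standardized difference of about (1.96 + 1.28) × √(2 × 0.75/40) = 0.63. With Holm, power in the plan's own model at the six-test level falls to 0.73 at N = 99 and 0.84 at 120 completers; if the family is all 18 comparisons, the corresponding level gives 0.60 and 0.75. The remaining changes are wording.
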